## 2. Materials and Methods

### 2.1. Study Design and Setting

The design is a randomized controlled two-arm trial.

Patients will be recruited from the university clinic from Universidad Católica San Antonio de Murcia, University of Malaga and schools nearby in Spain. They will be randomized to one of the two groups, each receiving a different intervention. The schedule to follow while carrying out this RCT can be found in Appendix A. The total period intended to be allocated to this study is from September 2023 to February 2025.

To randomize the sample, a Microsoft Excel spreadsheet will be used where a random assignment sequence will be generated. Each patient will be given a consecutive number in order of arrival and allocation concealed in envelopes.

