## Abstract

Pediatric flat foot (PFF) is a very frequent entity and a common concern for parents and health professionals. There is no established definition, diagnostic method, or clear treatment approach. There are multiple conservative and surgical treatments, the implantation of foot orthoses (FO) being the most used treatment. The evidence supporting FO is very thin. It is not clearly known what the effect of these is, nor when it is convenient to recommend them. The main objective of this protocol is to design a randomized controlled trial to determine if personalized FO, together with a specific exercise regimen, produce the same or better results regarding the signs and symptoms of PFF, compared to only specific exercises. In order to respond to the stated objectives, we have proposed a randomized controlled clinical trial, in which we intend to evaluate the efficacy of FO together with strengthening exercises, compared to a control group in which placebos will be implanted as FO treatment along with the same exercises as the experimental group. For this, four measurements will be taken throughout 18 months (pre-treatment, two during treatment and finally another post-treatment measurement). The combination of FO plus exercise is expected to improve the signs and symptoms (if present) of PFF compared to exercise alone and the placebo FO group. In addition, it is expected that in both conditions the biomechanics of the foot will improve compared to the initial measurements.

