## 1. Introduction

Pediatric flat foot (PFF) is a very frequent syndrome in primary care consultations, and it is also a shared concern among parents and professionals. Currently, there is no clear definition for the diagnosis of PFF, no treatment protocol, nor solid scientific evidence on the wide range of treatments [1,2].

PFF is characterized by a talocalcaneal misalignment, which is reflected as a collapse of the medial longitudinal arch (MLA) in a standing position [3]. Consequently, there is excessive pronation, accompanied by a drooping of the navicular. Some feet are also accompanied by calcaneal valgus [4]. All these alterations in the morphology of the foot force the rest of the structures, such as soft tissues or joints, to compensate for the excessive forces that act on the MLA [5]. These compensations cause an inefficient gait and symptoms such as pain, fatigue, stumbling when walking, problems in the proximal joints and reduced quality of life [6,7].

Diagnosis is based on clinical findings, including a variety of clinical tests and radiographic signs, these being considered the “gold standard” [6,8,9].

Regarding treatment, there are both conservative and surgical options, surgical being the last treatment option [10]. The most common conservative treatment is the use of foot orthoses (FO), where previous studies have concluded that they improve the results of some clinical tests, radiographic angles and symptomatology [11,12,13,14,15,16,17]. The purpose of the FO is to modify the position of the axis of the subtalar joint, decrease the speed of pronation, support the MLA and distribute loads more effectively [18,19]. Previous systematic reviews indicate that FO are beneficial and create positive changes in the development of the child’s foot [8,20,21]; these changes being greater in earlier ages of the treatment [22]. The exact age to start treatment is not clear, although it is recommended to start at preschool age (under 7 years old) so that the possibility of correcting the PFF is greater [23,24]. It has also been seen that the combination of FO with exercises is much more beneficial [25]. However, other studies indicate that the modifications that occur are those resulting from the natural development of the foot [26,27]. The evidence regarding the use of FO still does not present a consensus [20,28,29].

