Therefore, there is a discrepancy between treating and not treating PFF. There are authors who conclude that it is not necessary, since the natural evolution of the foot is that the MLA begins to form at 3–4 years of age and ends at 10 years of age [26,27]. A recent meta-analysis [30] concludes that, due to the normal development of the foot, treatments should be ruled out unless there are symptoms such as pain, limited function or reduced quality of life. However, other authors recommend early treatment, based on the fact that flat feet persist in 23% of adults and may be associated with Achilles tendinopathy, plantar fasciopathy, tibial posterior tendinopathy, hallux rigidus, chondromalacia patellae or patello-femoral pain syndrome [1,2,7,13,20]. Based on these latest data, it would be unethical to leave these types of feet untreated. Additionally, a recent systematic review [24] demonstrated that FO are beneficial, with evidence regarding efficacy in treating signs and symptoms.

Therefore, since PFF is a very common syndrome which, if left untreated, could cause problems in the long term and there is no consensus on the treatment protocol, it is necessary to investigate the effectiveness of FO in terms of improvement of the signs and symptoms, including the prevention of pathologies or injuries and the improvement of the quality of life. Sagat, P et al. have shown that children with flat feet presented poor performance in certain physical tasks, in contrast to a control group with neutral feet [31]. In addition, since it is a subject of great interest for researchers, health professionals and parents, it is necessary to carry out an investigation to assess the effectiveness of FO, with a standardized diagnostic protocol with validated tests in a larger sample size than previously published studies and with a longer-term follow-up. Furthermore, as the authors Zhang J. et al. pointed out, early identification of PFF is necessary; thus an intervention plays a crucial role in enhancing the outlook. Also, there is an absence of consistent quantitative standards for diagnosing flexible flatfoot [32].

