Therefore, the objective of the current study is to design a protocol for a randomized controlled trial (RCT) to determine whether personalized FO together with a specific exercise regimen produce the same or better results regarding the signs and symptoms of PFF, compared to only specific exercises. In addition, as specific objectives, to detect whether the possible bias that has prevented previous studies from demonstrating the efficacy of FO is due to the fact that these FO were not personalized; to define the PFF and to evaluate if there is a correlation between the clinical methods and the diagnosis and severity of the PFF.

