### 2.2. Eligibility Criteria

Subjects aged 3 to 12 years diagnosed with PFF. For the diagnosis of the PFF, the following criteria must be met:Foot Posture Index (FPI) > 6 [33].Navicular drop > 10 mm [34].Relaxed calcaneal stance position (RCSP) 6° to 12° valgus [35].Pronation angle > 10° [36].Arch index > a 1.35 [37].Double/single heel rise test negative [38].Windlass test negative [39].

In addition, the signature of the parents or legal guardians with consent to participate in the study will be necessary (Appendix B).

Participants will be excluded if they have undergone any surgery in the lower limbs, have previously received treatment for PFF, present osteoarticular injury, foot fractures or in the lower limbs in the last 6 months, ankle sprain, asymmetry, systemic diseases with osteoarticular involvement that present symptoms in the lower limb with gait disturbance (for example, Perthes disease) or biomechanical alteration of the lower limb with repercussions on the foot and ankle. Children suffering from any type of neurological or systemic disability (cerebral palsy, Down Syndrome, clubfoot or equino-varus, …) will also be excluded.

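### Children aged 3 to 12 are allocated from what reads as one unstratified list, although the background links age to arch development and to orthosis response, so chance age imbalance is left uncontrolled

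*Protocol article*

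**What the plan says.** Eligibility (section 2.2) is wide: "Subjects aged 3 to 12 years diagnosed with PFF". On allocation, section 2.1 says that "a Microsoft Excel spreadsheet will be used where a random assignment sequence will be generated", and continues: "Each patient will be given a consecutive number in order of arrival and allocation concealed in envelopes". It names no stratification factor and no blocking.

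The Introduction gives age two roles. On response to orthoses, it cites systematic reviews that found positive changes, "these changes being greater in earlier ages of the treatment"; it calls the right starting age unclear and mentions a recommendation to begin before 7. On natural history, it cites authors for whom "the MLA begins to form at 3–4 years of age and ends at 10 years of age".

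Section 2.7 describes a bivariate hypothesis test of control against experimental group, without an age term. Linear regression is listed only in general terms. Section 2.4.2 records age in months.

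**The concern.** Flat foot at 4 and flat foot at 11 may have different natural courses, and the Introduction itself says that some authors explain apparent orthosis benefit by natural development. That is the rival explanation the trial has to exclude. If one arm happens to receive more young children, part of the difference between arms may reflect development rather than the device, or may hide a device effect. A pooled bivariate test does not separate the two.

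Allocation also differs from most analysis detail in one respect: it is fixed when children are enrolled. A later analysis plan can add an age term but cannot add age strata to a list already in use.

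**Working it through.** **Inputs from the protocol article.** Ages 3 to 12 (2.2); 84 per arm randomised and 64 per arm before losses (2.6); age cut of 7 years (Introduction).

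**Inputs assumed.** Ages evenly spread, because no age distribution is given. The range is read either as 3 to 12.0 years (width 9, share under 7 = 4/9) or as 3 up to the 13th birthday (width 10, share 4/10). Simple 1:1 allocation.

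**The plan's own figure.** The article gives no figure on age. For a benchmark effect I use 0.5 SD, because 64 per group is what a two-sided t-test needs for 0.5 SD at 80% power (63.8). The inputs stated in 2.6, a difference of 2 with SD 1, would need only about 6 per group. That discrepancy is a separate matter.

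**Share under 7.** SE of the difference = √(2·p·(1−p)/n).
- n = 84, p = 4/9: √(2 × 0.444 × 0.556/84) = 0.077; P(gap ≥ 0.10) ≈ 19%. With p from 30% to 50% it is 16–19%.
- n = 64, p = 4/9: √(2 × 0.444 × 0.556/64) = 0.088; P(gap ≥ 0.10) ≈ 25%.

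**Mean age.** SD of a uniform age = width/√12, that is 9/√12 = 2.60 or 10/√12 = 2.89 years. SE of the difference = SD × √(2/n).

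| | 84 per arm | 64 per arm |
|---|---|---|
| SE of difference in mean age | 0.40–0.45 y | 0.46–0.51 y |
| P(gap ≥ 0.5 y) | 21–26% | 28–33% |
| P(gap > 1 y) | 1–2% | 3–5% |

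A simulation of 40,000 allocations on the same assumptions agrees: 18–19% and 24–25% for the 10-point gap, and the same ranges for mean age.

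**How far a gap could move the result.** Half a year is 0.5/2.60 = 0.19 SD of age. If the outcome is linear in age with correlation r, the arm difference shifts by r × 0.19 SD of the outcome, so by at most 0.19 SD. The article does not give r.

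**What an age analysis could deliver.**
- Evaluable under-7s per arm: 64 × 4/9 ≈ 28. The 95% half-width for the arm difference in that stratum is 1.96 × √(2/28.4) ≈ 0.52 SD. Using all 84 randomised would give 0.45 SD, but that ignores the 30% loss in 2.6.
- Interaction SE = √(2/(n·p) + 2/(n·(1−p))) in SD units. With 59 to 64 evaluable per arm (84 × 0.7 = 58.8) and 30–50% under 7, power is 24–29% for an interaction of 0.5 SD and 70–81% for 1.0 SD.
- An interaction of 0.5 SD with an even age split needs about 252 evaluable per arm for 80% power.

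**The case against.** **No objective concerns age.** A reader might infer that the trial fails to answer its own question, because the Abstract says it is not known "nor when it is convenient to recommend them". That is a gap in knowledge, not an aim. The main objective is "to determine whether personalized FO together with a specific exercise regimen produce the same or better results", and the specific objectives concern personalisation, the definition of flat foot, and the correlation of clinical methods with diagnosis and severity. This objection stands in full.

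**The age gradient is reported, not adopted.** The Introduction attributes it to cited reviews and adds that there is no consensus. Arch formation ending at 10 is the argument of authors who oppose treatment, and the protocol sets adult persistence of flat foot against it. It does not follow that the protocol regards orthoses as inactive at 10 to 12, and pain is also an outcome. This stands too; the point needs only that age is plausibly linked to change.

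**Low power for the pooled test is not shown.** If the effect were 0.50 SD under 7 and nil above, the pooled effect would be 0.50 × 4/9 = 0.22 SD, with power about 24% at 64 per group. The nil effect from age 7 appears nowhere in the article. With 0.25 SD above 7 the pooled effect is 0.22 + 0.25 × 5/9 = 0.36 SD and power about 53%; with 0.40 SD above 7 it is 0.44 SD and about 70%. The 24% therefore comes from the assumption.

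**A condensed article may omit detail.** Subgroup and interaction plans commonly sit in an analysis plan, so their absence here is not a fault. The allocation procedure, however, is described step by step, and as described it is one list. If the full protocol does stratify by age, the point falls.

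**Chance imbalance is already covered by the 5% error rate.** True, over repeated trials. Control of age improves precision and protects the reading of the one trial that will be run.

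**Conclusion.** The point holds as an inexpensive design improvement, not as an error that threatens the trial. The background makes age a plausible driver of both natural improvement and response, and the allocation described does nothing to balance it. On the even-age assumption, an imbalance of 10 points in the under-7 share has about a one-in-five to one-in-four chance, while a large gap in mean age is unlikely. The sizes depend on the true age mix at recruitment.

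The documents do not support two stronger readings: that imbalance would invalidate the comparison, or that the trial could establish at which ages orthoses work if only it were stratified. At the planned size, an analysis by age can be exploratory only.

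**What to change.** 1. Generate the allocation sequence as permuted blocks of varying size within two age strata, under 7 and 7 or over (the cut the Introduction already mentions), with a separate series of concealed envelopes for each. This has to be in place before the first child is allocated.
2. Include the age stratum, or age in months, in the between-arm comparison. Age is already collected. If enrolment has begun on the single list, this step still applies and covers most of the concern.
3. Prespecify, labelled exploratory, one table with the between-arm difference and its 95% confidence interval in each age stratum, and the age-by-arm interaction. State beside it that precision is limited.

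Cost: two lists instead of one, and one extra table of limited precision. There are no additional patients or visits, and the sample size does not change. Stratifying by clinic as well is optional; the argument here does not call for it.

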#### 2.4.1. Qualitative or Categorical Variables:

Gender: masculine or feminine.Pain: symptomatic or asymptomatic.Level of physical activity: high-low-nil.Double/simple heel rise test: Standing on toes with two legs/one leg for 25 repetitions. It will be considered positive if the participant is incapable due to fatigue or if when raising the calcaneus does not present a varus position [38].Supination resistance test: high-moderate-low. The patient is instructed to stand relaxed without any attempt to move the foot or lift the arch. The examiner’s fingertips are then placed plantar to the medial half of the navicular, and the examiner exerts a significant lifting force on the navicular. A normal foot will demonstrate subtalar joint supination with minimal lifting force. A pes valgus deformity will need extreme amounts of lifting force in order to produce little, if any, subtalar joint supination motion [40].Subtalar joint axis: Lateralized-neutral-medialized. The center of the neck of the talus should be located and marked to see the lateralized or medialized point, or if, on the contrary, it stops at the 2nd finger, which would indicate that it is neutral [36].Shoe wear at heel level: medial-center-lateral.Maximum pronation test: Positive or negative. The patient is asked to try pronate as much as possible; it is considered positive when performing the maneuver, the calcaneus cannot pronate more than 2° [41].Forefoot: adduction-neutral-abduction position [36].Foot posture index (FPI): Normal = 0 to +5; pronated = +6 to +9; highly Pronated = +10 to +12; supinated = −1 to −4 and highly supinated = −5 to −12. The six clinical criteria assessed: 1. palpation of the talus head; 2. lateral supra and inframalleolar curvature; 3. position of the calcaneus in the frontal plane; 4. prominence of the talonavicular region; 5. congruence of the internal longitudinal arch and 6. abduction/adduction of the forefoot with respect to the rearfoot. As we observe them, the following score is given: neutral = 0; clear signs of supination = −2; clear signs of pronation = +2 [33].Test of windlass: Positive or negative. It will be considered positive if, when performing dorsiflexion of the hallux, there is not supination of the foot, plantarflexion of the 1st ray, increase in the MLA and internal rotation of the tibia [39].Beighton scale: Hypermobility or normal. Subjects are rated on a 9-point scale, considering 1 point for each hypermobile site. These 9 points are: 1-hyperextension of the elbows (more than 10°), 2-passively touch the forearm with the thumb, having the wrist in flexion, 3-passive extension of the index finger to more than 90°, with the palm of the hand resting on the bed, 4-hyperextension of the knees (10° or more), patient in supine position and 5-flexion of the trunk forward touching the ground with the palms of the hands by bending without bending your knees. To be considered as hypermobile, it is required to have 4 points or more of the total of 9 [42].Podoscope: pronated-supinated-neutral [36].Pressure platform: maximum pressure zone, location of the center of gravity, gait progression line [43].

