### 2.6. Sample Size

The calculation of the sample size has been carried out with the data analysis program EPIDAT https://www.sergas.es/Saude-publica/EPIDAT?language=es (accessed on 4 August 2023). For the calculation, a clinical variation of 2 and a standard deviation of 1 have been considered. A statistical power of 80% and a significance level of *p* < 0.05; 95% confidence level. The minimum size would be a sample of 128 subjects (64 in each group randomly distributed). Considering that the loss rate could be 30%, the final size should be 84 subjects in each group. The total sample size should be 168 subjects.

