### 2.7. Statistical Analysis

The description of data will be calculated using the percentages and frequencies of the qualitative variables and for the quantitative variables, the standard deviation and the mean. In addition, in case of presenting high deviations, the measures of central tendency would be calculated, as is the case of the mean, median or mode. All this will be carried out in frequency distribution tables of different categories, using SPSS (IBM SPSS Statistics: V.28, USA).

It is intended to compare the dependent variables with the independent ones. The Kolgorov–Smirnof test (the adjustment to the normal of the distribution) will be used to check the normality of the quantitative variables; in the event that they follow a normal distribution, the following techniques would be used: linear regression or Pearson correlation for the comparison of quantitative variables, chi-square (X^2^) to compare qualitative variables and Student’s *t* or ANOVA to compare qualitative with quantitative variables. In the event that they do not conform to the normal, it will be calculated according to the case; the Wilcoxon test, the Kruskal–Wallis test, and the Mann–Whitney test.

To determine that the supposed differences between control group and experimental group are not due to a random error, but to a real difference, in the bivariate analysis a hypothesis test will be carried out. The significance level of p shall be 0.05.

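### One arrival-order sequence and bivariate tests ignore site although two universities recruit; if both randomise and assess children, the orthosis comparison loses precision but is not biased

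*Protocol article*

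**What the plan says.** Section 2.1 of the protocol article gives the sources of children: "Patients will be recruited from the university clinic from Universidad Católica San Antonio de Murcia, University of Malaga and schools nearby in Spain". It then describes the allocation: "a Microsoft Excel spreadsheet will be used where a random assignment sequence will be generated". The next sentence adds: "Each patient will be given a consecutive number in order of arrival and allocation concealed in envelopes". No stratum, block or per-site list is described.

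Section 2.7 says of the difference between control and experimental group that "in the bivariate analysis a hypothesis test will be carried out". For a quantitative outcome the named tests are Student's t or "ANOVA to compare qualitative with quantitative variables", with rank tests if normality fails. Categorical outcomes get chi-square. Linear regression is named only for relating quantitative variables to each other.

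Sections 2.4.1 and 2.4.2 list many measures that depend on the examiner. In the supination resistance test, for example, "the examiner exerts a significant lifting force on the navicular". The six FPI items, the marking of the subtalar axis, the calcaneal and tibial bisections and the navicular drop are also judged or marked by hand.

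**The concern.** Examiners at different places may score hand-performed foot tests at different levels. If children are randomised and assessed at both universities, site is then a foreseeable source of outcome variance. The allocation as described does not balance it, and a bivariate test of arm against outcome cannot remove it. The variance stays in the error term of every between-arm comparison, and in the trial actually run one arm may hold more children from the higher-scoring site. Power is at stake, together with how closely the orthosis effect can be estimated.

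**Working it through.** **The plan's own figure.** Section 2.6 states that "a clinical variation of 2 and a standard deviation of 1 have been considered", with 80% power and a 0.05 level, and arrives at 64 per group. The normal formula n = 2(1.96 + 0.84)²/d² with d = 2/1 gives 3.9, so 4 per group (about 6 by the exact two-sided t test), not 64. The 64 appears at d = 0.5: the formula gives 63 and the exact t test 63.8, so 64, with power 80.1%. That mismatch is a separate matter. Here it only explains why d = 0.5 is the working effect.

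**Assumptions, because the documents give no figures.** Two sites of equal size; an effect of 0.5 within-site SD; a constant gap g between sites, in within-site SDs.

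**Power without a site term.** With site share p = 0.5, total variance is inflated by 1 + g²·p(1 − p) = 1 + g²/4, and the effective d is 0.5/√(1 + g²/4).

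| Site gap g | Inflation | Site share of variance | Effective d | Power, 64 per group | Power, 58 per group |
|---|---|---|---|---|---|
| 0 | 1.000 | 0% | 0.500 | 80.1% | 76.1% |
| 0.5 | 1.0625 | 5.9% | 0.485 | 77.7% | 73.6% |
| 0.8 | 1.160 | 13.8% | 0.464 | 74.1% | 69.8% |
| 1.0 | 1.250 | 20.0% | 0.447 | 70.9% | 66.6% |

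The 58 column is what remains of the planned 84 per group after the stated 30% loss (84 × 0.70 = 58.8). At g = 1.0, restoring 80% power without a site term takes about 64 × 1.25 = 80 per group.

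**With and without a site term, simulated** (8,000 trials per setting, 64 per group, gaps from 0 to 1.0 SD). Type I error without a site term was 4.7% to 5.4%. For gaps of 0.46 to 1.0 SD, power with a site term was 78.8% to 79.8%; without one it was 77.3% down to 70.6%.

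**Chance imbalance.** With 84 of 168 children at each site and exactly 84 per arm, the between-arm difference in site share has an SD of 7.7 percentage points. It reaches 10 points in 16% of trials and 15 points in 4%. Under simple randomisation it exceeds 10 points in about 19% and 15 points in about 5%.

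**Imbalance and noise are one effect.** At g = 1.0 and 84 per arm, the variance of the arm difference is 2/84 = 0.0238 within sites and 1.25 × 2/84 = 0.0298 in total. The excess is 0.0060, whose square root is 0.077 SD. That equals the SD of the imbalance (0.077) times the 1.0 SD gap. The ordinary standard error therefore already carries the imbalance, and the two must not be added together.

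**If the planning SD already includes site variance,** power without a site term stays at 80%. A site term would raise it to about 82%, 84% or 88% when site explains 5%, 10% or 20% of the variance.

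**The case against.** The premise is inferred. Section 2.1 names places of recruitment and does not say that children are randomised, assessed or fitted at more than one of them. Some wording suggests one working clinic: a single podiatrist in 2.3.1, one clinic to contact in Appendix C, one pressure platform and one podoscope in Appendix D, one ethics committee in 2.8. Section 3.2 speaks of evaluators in the plural, so the question stays open. This stands, and it makes the point conditional.

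Unstratified allocation in concealed envelopes is valid, and a condensed article may leave stratification and covariates to a fuller document. That is fair for what the article omits. But it does state how numbers are assigned and what kind of test compares the arms, and both take no account of site.

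Stable site offsets would cancel in change from baseline, and every child has a baseline measurement. That would remove much of the loss, but 2.7 does not say that change is analysed. Pain scores, footprint indices and platform loads also depend less on the examiner.

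Three stronger readings are tempting and are not supported:

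- A reader might infer that an apparent orthosis effect would partly be an examiner effect, in the sense of confounding. In a single trial a large imbalance can shift the estimate: 15 points at a 1.0 SD gap moves it by 0.15 SD. That pairs the largest assumed gap with an imbalance seen in about 5% of trials, and the standard error already allows for it. At a 0.5 SD gap a typical imbalance moves it by about 0.077 × 0.5 = 0.04 SD.
- A reader might count the schools as further sites. The document shows them only as sources of recruits.
- A reader might infer that two children would receive the same number. That supposes separate counters at each place, which 2.1 does not describe, and nothing excludes a shared register.

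**Conclusion.** The point holds as a conditional loss of precision that is worth correcting. The allocation and the between-arm analysis, as stated, take no account of site although two universities recruit and many outcomes are examiner-scored. If both universities randomise and assess, the cost at 64 per group is about 2, 6 or 9 points of power for site gaps of 0.5, 0.8 or 1.0 SD. This rests on two equal sites, a within-site effect of 0.5 SD and a planning SD that excludes site variance; none of these is given in the documents. With one assessing team the loss is near zero. Where the planning SD includes site variance, the plan keeps its 80% but forgoes the gain a site term would bring. The validity of the test is not in question.

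**What to change.** In 2.1, prepare for each randomising university its own concealed permuted-block list, with varying block sizes, and its own numbered envelope set. In 2.7, include site as a factor in the between-arm analysis: a linear model for quantitative outcomes, and a site-stratified or logistic analysis for categorical ones. If all children are randomised and assessed at one clinic by one team, a sentence in 2.1 saying so settles the matter instead.

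The cost is a second spreadsheet list, slightly more envelope handling and one degree of freedom for two sites. Blocking makes some assignments more predictable, which the varying block sizes limit. The lists have to be set up before enrolment starts.
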